## Abstract

Background: As a higher-risk group of postpartum depression (PPD), rural to urban floating women urgently require effective and accessible mental health care after childbirth to prevent PPD. Even though there were various interventions, only a small number of women have sought professional help to reduce their depressive symptoms after childbirth, suggesting the need for an innovative intervention delivery to overcome women’s help-seeking barriers. Online and offline (OTO) interventions, which combine face-to-face and internet-based interventions, provide apparent benefits. As a result, the protocol for a randomized controlled study (RCT) was designed to examine the effectiveness and acceptability of OTO intervention on psychosocial outcomes for Chinese rural-to-urban floating women including the reduction of PPD symptoms and PPD stigma, and the improvement of social support and quality of life. Methods: A double blind, multicenter, RCT will be used and a total of 226 participants will be recruited. The OTO intervention called the “Hi, Mom” program will integrate two face-to-face consulting sessions with online sessions comprising an information module, a communication module, an ask-the-expert module, and a peer story module over a period of three months. The control group will receive routine postpartum care. Outcome measures including PPD symptoms, PPD stigma, social support, quality of life, mother–child bonding, and satisfaction with health care received will be conducted at baseline, postintervention, and three-month follow-up. Results and Discussion: If the intervention is effective, it will provide a convenient and effective intervention program on postpartum mental well-being for rural-to-urban floating women. As the first study to test the effects of an OTO intervention for the prevention of PPD in China, the outcomes gained from this study will provide evidence-based knowledge for clinical practice on PPD prevention based on online and offline health technologies. Moreover, it could be used to plan a culturally appropriate OTO intervention for migrant mothers from different countries.

## 1. Introduction

Postpartum depression (PPD) is defined as any major or subclinical depression occurring in women after childbirth [1]. In the recent ten years, PPD has become one of the severe worldwide public health problems [2,3], and its incidence rate varies from about 20% in developed countries to 25% in developing countries [4]. In addition to the high prevalence, PPD was identified to have adverse effects on the physical and mental health of women [3], the cognitive and emotional development of babies [5], and the bonding of family members [6]. In consideration of the negative consequence of PPD, it is of significance to carry out efficient and timely interventions [7].

Systematic review and meta-analysis found from [7,8,9,10] that there have been various interventions for PPD, i.e., pharmacological interventions and nonpharmacological intervention. Although pharmacological method is an effective treatment for depression, mothers are often reluctant to take antidepressant medication due to concerns about breast milk transmission or potential side-effects on their babies [8,11]. Thus, it is important to evaluate the effects of nonpharmacologic interventions on postpartum women experiencing PPD. In the existing literature, psychosocial intervention [11,12,13,14,15] and physical intervention [16,17,18,19] have been identified to be associated with a reduction in the likelihood of continued PPD, which mainly used traditional face-to-face method.

Despite the existence of these traditional interventions, there have been few women with PPD seeking professional help [7,20]. For instance, a cohort study including 1126 women in Hunan, China, found that only 9.3% of women at a high risk of PPD chose professionals as their first option [21]. Another study revealed that only 13.6% of Portuguese women with PPD sought professional help to address their emotional difficulties during the postpartum period [22]. Actually, some factors hindered the feasibility and generalizability of these traditional interventions. Firstly, the shortage of health professionals negatively affected the accessibility of traditional mental health services [23,24]. Secondly, the stigma on PPD blocked women seeking face-to-face help, which was particularly prominent in developing countries [25]. Thirdly, time and financial constraints and struggles with parenting babies were the other obstacles of women in attending traditional face-to-face intervention [24]. These barriers indicated the urgent need for a new form of intervention to improve the access of postpartum women.

E-health technology was the innovative approach of intervention delivery that uses online technology [26], with the distinguished advantages of improved flexibility, accessibility, and reduced financial and time cost [27]. The random-effects model of a recent meta-analysis indicated that the internet-based interventions have proven to be effective in the reduction of PPD symptoms (d = 0.642, N = 7) [13]. However, all the seven randomized controlled trials (RCTs) for PPD based on internet had been conducted in developed countries, such as UK, USA, Canada, Australia, and Sweden [13]. Furthermore, some researchers argued that internet-based interventions had obvious drawbacks of low diagnosis accuracy, and engagement and response rates due to the absence of face-to-face support and assessment from health professionals during the whole intervention [28,29,30]. Moreover, internet-based intervention lacked important opportunities to provide customization for ensuring relevance [31]. Thus, online intervention can be a significant supplement of traditional interventions, rather than replacing them [32].

Online and offline (OTO) intervention combines face-to-face (meaning directly meeting someone in the same place and allowing for the full potential of nonverbal communication) therapy with internet-based interventions, which can be integrated and sequentially conducted. Previous research verified that the blended OTO intervention had positive outcomes on some psychological disorders, such as depression [31,33,34], and was highly accepted by patients [35]. To the best of our knowledge, no RCTs by online and offline intervention have been conducted targeting PPD in China.

During the last three decades, there have been a great number of people moving from rural areas to urban areas owing to the rapid development of the economy and urbanization in China [36,37]. These special people, called “floating population” or “internal migrants”, are approximately 247 million, accounting for almost one-fifth of the total population in China [38]. Reports said almost half of floating populations were women, and the majority of them were in childbearing age [39,40]. In comparison with city residents, these floating women had characteristics of a younger childbearing age, having lower educational levels, and poor living and working environments [39,40].

Evidence indicated that health inequality has obviously existed between the city residents and the floating women due to the imbalance of health resources allocation [41,42]. Prior studies found that floating women were prone to encountering more mental problems and receiving less social support during the postpartum period in comparison with city residents [43,44,45]. For example, the mean EPDS (Edinburgh Postnatal Depression Scale) scores among rural-to-urban floating women at 6 and 12 weeks postpartum were 11.19 (4.89) and 11.18 (5.34), respectively [45]; much higher than the corresponding results of 9.09 (4.33) and 8.63 (4.41) from city resident women [46]. International research had similar findings that the incidence of PPD in American mothers who are of nondominant culture and socioeconomically disadvantaged had three to four times higher scores than in women from the general population [47].

As a higher-risk group of PPD, rural-to-urban floating women urgently require effective and accessible mental health care after childbirth; and the future tailored, evidence-based intervention is highly needed to improve these women’s psychological well-being and social support during the postpartum period [44,45]. Therefore, the protocol for a randomized controlled trial was designed in the research to examine the acceptability and effectiveness of an online and offline (OTO) intervention for PPD prevention among rural-to-urban floating women.

## 2. Methods

### 2.1. Aim

The purpose of this study was to examine the effectiveness of OTO intervention on psychosocial outcomes for Chinese rural-to-urban floating women, including the reduction of depression symptoms and PPD stigma, and the improvement of social support, quality of life, and satisfaction.

We hypothesized that compared with floating women in the control group; participants in the intervention group will be reported to have the significant differences:(1)Reduced PPD symptoms and stigma;(2)Improved social support, quality of life, and mother–child bonding;(3)Great satisfaction with health care received during the postpartum period.

### 2.2. Design

A double blind, multicenter, randomized controlled trial (RCT) was designed in the research. The SPIRIT 2013 Statement and the guidelines for the Standard Protocol of Clinical Trials are strictly followed.

### 2.3. Participants

Participants who meet the inclusion criteria will be recruited. The inclusion criteria are: (1) rural-to-urban floating women; (2) ≥18 years old; (3) married; (4) women with an EPDS (Edinburgh Postnatal Depression Scale score) of 10 or more; (5) women with access to the internet. The exclusion criteria are: (1) having depression history; (2) with a serious physical or mental condition of either the mother or the infant; (3) undergoing psychotherapy or any other physical or psychological intervention.

### 2.4. Study Setting and Recruitment

The research will be conducted in the maternity wards of three affiliated hospitals in X University, where each hospital has an annual baby-birth record of more than 4000. All women admitted in the wards will be approached by researchers to ask their willingness and will be measured by the EPDS before recruitment. If they have an EPDS of 10 or more, they will be eligible to participate in this study. The information sheets, posters, and leaflets will be used to introduce the purposes and process of the research before recruitment. If rural-to-urban floating women meeting the inclusion criteria are willing to participate, they will be asked to sign an informed consent form and be informed of freedom to withdraw whenever they want. The CONSORT (consolidated standards of reporting trials) [48] flowchart is illustrated in Figure 1. The recruitment period is expected to extend over a 3-month period. Recruitment of participants began in May 2022. Primary endpoints (baseline and postintervention), follow-up measure (three months), and data analysis are expected to be complete in January 2023.

### 2.5. Sample Size

The study sample size will be determined by the primary outcome of PPD, with the standardized effect size of 0.35 for PPD (EPDS scores) reported in a previous PPD trial [49,50]. A sample of 180 women (90 women per group) will be needed to detect an effect size of at least 0.35, with 80% power, two-sided *p* < 0.05, which is calculated by inputting the above parameters in PASS (Power Analysis and Sample Size) software (NCSS company, East Kaysville, UT, USA). Assuming an attrition rate of about 20%, a minimum of 226 women (113 in each group) is required.

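### The stated inputs (effect size 0.35, 80% power, two-sided 0.05) need 130 women per group, not 90; 90 per group gives about 65% power

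*Protocol article*

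**What the plan says.** Section 2.5 (Sample Size) bases the size of the trial on EPDS alone: "The study sample size will be determined by the primary outcome of PPD". The effect size is taken from earlier work, "with the standardized effect size of 0.35 for PPD (EPDS scores) reported in a previous PPD trial". The conclusion reads: "A sample of 180 women (90 women per group) will be needed to detect an effect size of at least 0.35, with 80% power". The significance level is 5%, two-sided. The section also gives the source of the figure: "which is calculated by inputting the above parameters in PASS".

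The figure is then raised for dropout: "Assuming an attrition rate of about 20%, a minimum of 226 women (113 in each group) is required". The Abstract carries the total forward: "a total of 226 participants will be recruited". Section 2.6 sets 1:1 allocation.

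Section 2.5 gives no baseline correlation, no correlation between repeated measures and no covariate. It does not name the test that was sized.

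**The concern.** A standardized effect size, a power, a two-sided significance level and equal allocation are all that is needed to size a comparison of two means. Together they fix the answer, so the stated 90 per group can be checked directly. It looks too small for an effect of 0.35.

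EPDS is the primary outcome and the only basis for the sample size. If the power is overstated, a true effect of the assumed size is more likely to be missed than the protocol tells its readers. A non-significant result could then be read as evidence of no effect, on the strength of 80% power that the stated basis does not provide.

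**Working it through.** **Inputs** (sections 2.5 and 2.6): d = 0.35, two-sided alpha = 0.05, power = 80%, 1:1 allocation, 20% attrition, 90 analysed and 113 enrolled per group.

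**Attrition step.** 90 / 0.8 = 112.5, rounded up to 113 per group, or 226 in total. This reproduces.

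**Base sample size.** By the normal approximation, n per group = 2 × (1.960 + 0.842)² / d² = 2 × 7.85 / 0.1225 = 128.1, so 129. With the noncentral t, n = 129.1, so 130 per group and 260 in total. At 20% attrition, 260 / 0.8 = 325. The stated 90 does not reproduce and is 40 women per group short.

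**Power at the stated sizes.** Power ≈ Φ(d × √(n/2) − 1.960).
- n = 90: 0.35 × √45 = 2.348; Φ(0.388) = 65.1%. Noncentral t: 64.6%.
- n = 113, no dropout: 0.35 × √56.5 = 2.631; Φ(0.671) = 74.9%. Noncentral t: 74.5%.

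**Effect detectable with 80% power (noncentral t).** 0.420 at 90 per group; 0.374 at 113 per group.

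**Other readings of the inputs.** None gives 90 per group.

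| Reading | n for 80% power |
|---|---|
| One-sided 0.05 | 102 per group |
| Mann-Whitney test (efficiency 0.955) | about 135 per group |
| Paired or one-sample t-test | about 67 in total |
| 0.35 read as Cohen's f, two groups | about 67 in total |

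**Adjustment for baseline EPDS, one post-baseline score.** The required n is multiplied by (1 − ρ²), where ρ is the correlation between baseline and outcome. The documents give no ρ, so these values are assumptions.

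| ρ | n per group for 80% power | Power at 90 per group |
|---|---|---|
| 0.3 | 117.5 | 69% |
| 0.4 | 108.5 | 72% |
| 0.5 | 96.8 | 77% |
| 0.6 | 82.6 | 83% |

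Setting 129.1 × (1 − ρ²) = 90 gives ρ = √(1 − 90/129.1) = 0.55.

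**Effect of the entry criterion on ρ (illustration only).** Section 2.3 admits women with EPDS of 10 or more, which narrows the baseline range and lowers ρ. The Introduction gives a mean of 11.19 and SD of 4.89 for floating women at 6 weeks postpartum. Under a normal distribution with those values, a correlation of 0.5 before selection becomes about 0.35 to 0.36 after it. The baseline here is taken on the maternity ward and the starting 0.5 is assumed, so only the direction should be relied on.

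**The case against.** The strongest objection is that 65% is the power of a test the protocol does not plan for EPDS. Section 2.10 plans a repeated measures multivariate analysis of covariance over three time points and keeps the t-test for baseline comparisons and satisfaction. Table 2 schedules two post-baseline EPDS scores. If the effect were 0.35 at both, an analysis of their mean would do better:

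- Mean of the two scores, no baseline adjustment: n is multiplied by (1 + ρ)/2, which gives 83.9 per group at ρ = 0.3 and 90.4 at ρ = 0.4, so roughly 80% power at 90 per group.
- Mean adjusted for baseline, one common correlation ρ: the variance factor is (1 + ρ)/2 − ρ². At ρ = 0.2 this is 0.56 and power is 88%; at ρ = 0.5 it is 0.50 and power is 91%.
- Baseline correlation 0.36 and correlation 0.5 between the two later scores: the factor is 0.75 − 0.13 = 0.62 and power is 84%.

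This arithmetic is right, and two parts of the objection stand. The 65% must be labelled as t-test power, and the 0.55 threshold applies to a single post-baseline score. The objection does not rescue section 2.5. That section attributes 180 to the inputs it lists, and no correlation or averaging over time points is among them. Section 2.4 names baseline and postintervention as the primary endpoints, which points to one post-baseline score. The gain also depends on the effect persisting at 0.35 to the three-month follow-up, which the protocol does not claim. It could further be said that a condensed article omits software detail. The finding, though, is not that detail is missing, but that the inputs given do not produce the output given.

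**Conclusion.** The concern holds. The stated inputs require 130 per group, and 90 per group gives 64.6% power at an effect of 0.35, about 15 percentage points below the stated 80%. The chance of missing a true effect of 0.35 is therefore about 35%, roughly 1 in 3, instead of 1 in 5. All 226 women with no dropout would give 74.5%. These figures assume a two-sample t-test on EPDS, which is what the listed inputs describe.

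A more efficient analysis might reach 80% with 90 per group, but only under correlations the protocol does not state: about 0.55 with baseline if one post-baseline score is used, or suitable values if two are averaged. Even if such an assumption lay behind the 180, section 2.5 is wrong as written. Because the error concerns the power for the primary outcome, it must be corrected.

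**What to change.** Keep 226 and delete the claim that 90 per group detects 0.35 with 80% power. Replace it in section 2.5 with text such as: *With 90 analysed women per group, a two-sample t-test at two-sided alpha 0.05 has 65% power for a standardized EPDS difference of 0.35 and 80% power for 0.42.*

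If the primary analysis is to be EPDS adjusted for baseline, state power on that basis. Name the time point and write down the assumed correlation in the selected population. For one post-baseline score that is 77% at a correlation of 0.5, with 80% only from about 0.55. If both later scores are to be averaged, say so, and give the correlation between them and the assumed effect at each.

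The cost is rewording one section and accepting a less favourable stated power. No extra women are needed. Section 2.4 says recruitment began in May 2022, so the correction should be made before results are interpreted.

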### 2.6. Randomization and Blinding

Participants will be randomly assigned to the intervention group or control group with an allocation ratio as 1:1. Sequence randomization will be performed using a computerized random number generator, and its result will be kept in sealed and opaque envelopes and saved by the researchers who have no direct relationship with the project to make sure that the random allocation is masked in advance. During the research process, the group allocation will be blinded to the participants, enrolling researchers, outcome assessors, and data analysts.

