The “Hi, Mom” program of OTO intervention will integrate two face-to-face consulting sessions with online sessions including an information module, a communication module, an ask-the-expert module, and a peer story module over a period of three months. According to the self-efficacy theory, the mastery experiences of participants will be acquired by provision of the related PPD information via the information module, ask-the-expert module, and face-to-face consulting. Vicarious experiences of women can come from the peer support module where women may share their successful experience of dealing with PPD. Verbal persuasion can be gained from feedback, comments, and suggestions from health professionals in the ask-the-expert module and other mothers in the communication module. The physiological and emotional states can be improved through the above various supports, information and feedback in the information module, communication module, ask-the-expert module, peer story module, and face-to-face consulting. In terms of the social exchange theory, the structural social support, including the formal and informal social network of women, can be built; and various kinds of functional supports, such as informational support, material support, emotional support, and evaluation of support, can be provided from the health professionals and others through the designed information module, communication module, ask-the-expert module, peer story module, and face-to-face consulting.

The women in the control group will receive routine care, including health care from obstetricians and obstetric nurses during the hospitalization of three to five days; and at least two home visits from community health professionals [54]. The women in the intervention group will receive an OTO intervention called the “Hi, Mom” program and routine postpartum care. Table 1 describes the details of the “Hi, Mom” program.

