The online session of the “Hi, Mom” program is designed to have fixed structures, which lasts approximately three months. Four modules are incorporated to meet learning needs, communication needs, emotional needs, and evaluation needs for rural-to-urban floating women. The information module is the PPD learning forum about prevention knowledge and skills showed by multimedia resources. In consideration of the lower educational level of floating women, we prefer to use many more pictures and videos, rather than words. The related knowledge and skills include (1) How to understand PPD? (2) How to deal with negative emotions? (3) How to relax yourself? (4) How to combat the stigma? (5) When and how to seek help? (6) How to balance postpartum life and family relationship? (7) How to adapt to the role of a mom? 

The communication module, ask-the-expert module, and peer story module will provide women with opportunities for acquiring social networking and various kinds of supports. For example, the communication module provides a platform for new mothers to tell their own postpartum stories, exchange experiences with PPD, and seek empathy and belonging. This module also invites women to discuss some topics such as the experience of “Doing the month”, communication barriers, potential interpersonal conflicts after childbirth, and effective skills to solve emotional problems. The ask-the-expert module gives floating women opportunities of timely interaction with health professionals where experts can answer women’s questions within 24 h. Some self-testing tools are likewise included in the module to assist new mothers in self-assessing their state of mind. The peer story module is the last module where six mothers are invited to share their successful experience of overcoming PPD and provide role models for these floating women. 

Floating women in the intervention group will be taught to log in and use each online module of the “Hi Mom” program. Women will be required to log into the online sessions at least twice a week, totaling at least one hour per week; and their duration and frequency of logins will be monitored to evaluate an individual’s adherence. Technical assistance for the online program will be available from Monday to Friday by telephone or email.

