### 2.9. Data Collection

Baseline assessments will be conducted by the research team and participants will be asked to complete EPDS, STIG-9, PSSS, EQ-5D, PBQ, and sociodemographic and clinical data in the obstetric wards. Postintervention assessment will be performed immediately after intervention and follow-up assessment will be performed 3 months after intervention. At the two time points of postintervention and follow-up assessment, the questionnaires, comprising EPDS, STIG-9, PSSS, EQ-5D, PBQ, and the health care satisfaction questionnaire, will be sent to participants by WeChat or email, and the completed questionnaires will be returned to the researchers likewise by WeChat or email. In order to improve the response rate, a reminder telephone or WeChat will be given to participants before and after one week of the two time points, respectively.

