### 2.12. Validity and Reliability

The scientific and rigorous research design, i.e., the sound theoretical framework of intervention, a good representative and predetermined sample, and all the tools with a proven good reliability and validity, will be strictly executed to reduce bias effectively and enhance the generalizability of the research results beyond the target population. Furthermore, to ensure proper administration of the interventions, the related researchers will be trained before data collection. Moreover, the group allocation will be blind to the participants, enrolling researchers, outcome assessors, and data analysts in order to reduce the bias during the research process.

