## 3. Discussion

Nowadays, the high prevalence of PPD for rural-to-urban floating women [44,45] and the shortage of mental health service resources in China [23] make it extremely urgent to effectively intervene in PPD for floating women. Despite the existence of various interventions, only a small number of women have sought professional help to reduce their depressive symptoms after childbirth [21], suggesting the need for an innovative intervention delivery to overcome women’s help-seeking barriers. Online and offline (OTO) intervention is the combination of face-to-face treatment with internet-based interventions that have significant benefits [7]. On the one hand, it can have higher flexibility and accessibility, and reduced financial and time cost [27]. On the other hand, it likewise can offer significant customization via face-to-face communication and support [7]. Therefore, our research aims to examine the effectiveness and acceptability of an OTO intervention of the “Hi, Mom” program on psychosocial outcomes for Chinese rural-to-urban floating women, including the reduction of PPD symptoms and PPD stigma, and the improvement of social support and quality of life. To the best of our knowledge, no RCTs by OTO intervention have been conducted targeting PPD in China.

Despite the advantages of the research, some limitations need to be noted. Firstly, self-report tools will be used to measure PPD, and it may lead to social desirability bias owing to the traditional belief of “domestic shame should not be made public”. Secondly, this study will not conduct further follow-up after three months’ intervention due to the time and financial restrictions. Thirdly, some potential biases could be caused as blinding of researchers during the whole research process is not possible.

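### The double-blind label and the claim that participants are blinded do not fit a visible program compared with routine care and a self-rated EPDS

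*Protocol article*

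**What the plan says.** The design statement in section 2.2 of the protocol article is "A double blind, multicenter, randomized controlled trial (RCT) was designed in the research", and the abstract uses the same label. Section 2.6 specifies who is blinded: "During the research process, the group allocation will be blinded to the participants, enrolling researchers, outcome assessors, and data analysts". Section 2.12 repeats the list as a safeguard: "Moreover, the group allocation will be blind to the participants, enrolling researchers, outcome assessors, and data analysts in order to reduce the bias".

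On the two arms, section 2.7 says "The women in the control group will receive routine care, including health care from obstetricians and obstetric nurses" and "The women in the intervention group will receive an OTO intervention called the “Hi, Mom” program and routine postpartum care". For the online part, "Floating women in the intervention group will be taught to log in and use each online module". The same section and Table 1 add weekly reminder calls and two in-person consultations at home, and Table 1 names researchers as the providers.

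On measurement, section 2.8.2 makes the EPDS the primary outcome. Under section 2.9, the questionnaires after baseline "will be sent to participants by WeChat or email, and the completed questionnaires will be returned to the researchers". The Discussion describes the depression measures as self-report and also lists as a limitation that "some potential biases could be caused as blinding of researchers during the whole research process is not possible".

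**The concern.** Blinding of participants is claimed outright, and section 2.12 offers it as a protection against bias. Yet the arms differ in ways that every woman can see, and the women score the primary outcome themselves. A rater who knows her arm can let expectation, or the wish to please the team that visits and phones her, influence her answers.

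What is at stake is how a difference in EPDS may be read. Under a double-blind label, a reader would take differential reporting to be controlled and would attribute the difference to the program's effect on symptoms. In the design as described, that difference may also contain expectation and reporting effects, and the limitations do not say so. An article may leave detail to a full protocol, but this is not omitted detail. It is a positive statement that the rest of the article does not bear out.

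**Working it through.** No figure in the article bears on this point, so the check sets the statements side by side.

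**1. Can participants be blind to allocation?**

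| Feature | Intervention arm | Control arm | Source |
|---|---|---|---|
| Routine postpartum care | yes | yes | 2.7, Table 1 |
| Named program (Hi, Mom) | yes | no | 2.7, Table 1 |
| Log-in training and four online modules | yes | no | 2.7, Table 1 |
| Weekly calls prompting use of the program | yes | no | 2.7, Table 1 |
| Two consultations with researchers at home | yes | no | 2.7, Table 1 |
| Home visits by community health staff | as part of routine care | at least two | 2.7, Table 1 |
| Sham, attention control or alternative program | not applicable | none described | 2.7, Table 1 |

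Home visits alone might not reveal the arm, because controls also receive some. The program name, the log-in training, the online modules and the weekly calls would reveal it. Section 2.4 adds that the study's purpose and process are explained before consent. That women can tell their arm is an inference from the design, but a firm one, because nothing described would hide the difference.

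**2. Who rates the primary outcome?** The EPDS is a questionnaire (2.8.2) that the Discussion calls self-report. After baseline it goes to the woman and comes back by WeChat or email (2.9). No independent rater or clinical interview is described. The woman is therefore the rater. The other scales and the satisfaction questionnaire go out and come back by the same route.

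**3. What does blinding of outcome assessors then protect?** Staff who send reminders and who receive and score questionnaires can be kept unaware of the arm, which guards against differential chasing or handling. It does not act on the answers themselves, so it gives no protection for the EPDS score.

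**4. Does the Discussion already disclose the problem?** Its sentence covers researchers over the whole process. It does not mention participants. Sections 2.6 and 2.12 claim blinding for enrolling researchers and outcome assessors, and the Discussion does not say which researchers it excepts. As they stand, the three places leave open who is blinded.

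**5. Which parts of section 2.6 stand?** Concealment of the sequence in sealed, opaque envelopes held by people outside the project is not in question. Blinding of data analysts is feasible. The faulty elements are the participant claim and the label that rests on it.

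**The case against.** Several stronger readings are tempting, and the document does not support them.

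- **That the Discussion admits blinding is impossible and so flatly contradicts section 2.6.** It speaks of researchers only. Table 1 makes researchers the providers, and section 2.6 does not list providers among the blinded. The sentence can be read as a concession about providers. That leaves an ambiguity to be resolved, not a flat contradiction. The finding on participants rests on the described arms, not on this sentence.
- **That the protocol itself predicts bias from unblinding because it expects social desirability bias.** The Discussion ties this to a cultural reluctance to disclose family matters, which could act in both arms. It does not link it to knowledge of allocation.
- **That the bias can be sized.** One could set an assumed shift of 0.5 to 1 EPDS point against the planned 0.35 SD. With the 6-week SD of 4.89 quoted in the Introduction, 0.35 × 4.89 = 1.71 points, giving 0.5/1.71 = 29% to 1/1.71 = 58%. With the 12-week SD of 5.34, 0.35 × 5.34 = 1.87 points, giving 27% to 53%. The shift has no basis in the document, so the percentages merely restate the assumption. The SDs also come from floating women not described as restricted to an EPDS of 10 or more, which this trial requires.
- **That outcome assessors should be struck from the blinding statements.** This would discard a feasible protection in reminding, receipt and scoring.
- **That an unblinded comparison with routine care is itself a design error.** It is not; the error is the description.

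The best defence of the current text is that the consent material is not shown, so women might be told little about the other arm. Section 2.4 promises an account of purpose and process, not of each arm's content. This somewhat lowers the certainty that controls know what they are missing. It does not rescue the text, because section 2.6 claims blinding of group allocation, not merely of the hypothesis. No arrangement is described that would keep a woman enrolled in a named program from recognising it.

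It is also fair that the Discussion already discloses self-report and incomplete blinding of researchers. That disclosure stands, but it omits participants, whose knowledge matters most for a self-rated score.

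**Conclusion.** The concern holds for the double-blind label in the abstract and section 2.2, and for the participant-blinding claim in sections 2.6 and 2.12. Neither fits the arms described in section 2.7 and Table 1, and assessor blinding does not protect a self-rated EPDS. The Discussion does not disclose that participants are unblinded, and it must be reconciled with sections 2.6 and 2.12 by saying which researchers it means.

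The conclusion assumes that no sham or concealment procedure exists beyond what the article describes. The direction and size of any bias cannot be calculated from the document. The correction leaves data, endpoint, sample size and analysis untouched, but it limits what an EPDS difference can be said to show.

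**What to change.** - Abstract and section 2.2: remove the double-blind label.
- Sections 2.6 and 2.12: remove participants from the list of those blinded. State that the trial is open-label to participants and intervention providers and that allocation is concealed from enrolling staff until assignment. State also that data analysts, and the staff who send reminders and who receive and score questionnaires, are blinded. Identify those staff by role and keep them separate from the providers.
- Sections 2.8 and 2.9: state that the EPDS and the other outcomes are self-rated by women who are not blinded.
- Discussion: specify which researchers cannot be blinded. Add the lack of participant blinding as a limitation, say that the EPDS difference may include expectation or reporting effects, and word the conclusion accordingly.

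The cost is wording and a less favourable design label. The changes can be made although recruitment has begun. The one operational demand is that the staff named as blinded are in fact kept so.
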